### Study Design

The effects of Mindhelper will be evaluated in a 2-armed 1:1 RCT and complemented by qualitative insights from interviews with participants assigned to the intervention group. Figure 1 provides an overview of the study design.

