### Sample Size Calculation

We performed a sample size calculation, considering an average effect size of 0.1 for mental well-being (on the WHO-5 scale) at T2 to be of public health relevance (it is equal to an improved WHO-5 score of 1.94 points on average in the intervention group compared to the control group). Even small effects on individual mental health outcomes can lead to a major impact at a population level, particularly when the service can be scaled widely and reach a large target audience.

We applied the conventional levels of statistical power (0.8) and level of significance (.05) and assumed an SD of 19.4 at T1 among the intervention and control groups combined (based on data from the feasibility study) [18]. On the basis of these assumptions, at least 3142 participants were required (n=1571, 50% in each group).

In the test phase, we retrieved a response proportion of 64.1% (323/504) at T2 (primary end point). Assuming a similar retention proportion, we aim to include 4910 participants. The proportion of participants responding to the follow-up surveys will be regularly reviewed to evaluate if the assumption regarding retention in the sample size calculation is correct or if the number of participants included should be increased or decreased.

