#### The Effects of Mindhelper on Mental Well-Being and Psychological Functioning

The primary analysis will compare mean mental well-being, measured by WHO-5, between the intervention and control groups at T2, adjusted for WHO-5 scores at T1. If model assumptions are met, we will use a linear regression model. Psychological functioning, the secondary outcome measured by SWEMWBS, will be analyzed similarly as a continuous outcome, also adjusted for T1 values.

T2 was chosen for the primary assessment of effect because Mindhelper aims to provide immediate support and advice when problems arise. Most users visit thewebsite for a shorter period rather than regularly over multiple weeks. If the model assumptions are met, long-term effects will be evaluated at T3 and T4 using a repeated measures linear regression model.

To assess variation in effect by participants’ gender (male, female, or other) and socioeconomic background (parents’ highest educational attainment), analyses will be stratified accordingly. In addition, we will stratify by mental well-being at T1, expecting Mindhelper to be most effective for participants with moderate mental well-being (WHO-5 scores between 36 and 50) compared to those at high risk of depression or long-term stress (WHO-5 scores between 0 and 35) and those with mental well-being scores within the average range of the general population (WHO-5 scores >50). Furthermore, this stratified analysis will enable us to assess potential negative side effects of the intervention, assessing if the intervention group with WHO-5 scores >50 at T1 experienced a decline in mental well-being compared to the control group.

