#### The Effects of Mindhelper on Intentions of Help Seeking

To evaluate the impact of Mindhelper on help-seeking intentions, we will compare scores on the constructed scale between the intervention and control group at T3, adjusted for T1 values. Potential long-term effects will be assessed at T4 using a model accounting for repeated measures. We selected T3 for this evaluation because we hypothesize that changes in help-seeking intentions take longer to manifest compared to the primary and secondary outcomes.

The 8 categories of support will be assessed separately. Furthermore, we will categorize the sources into 3 groups: informal sources (categories 1, 2, and 3), formal sources (categories 4, 5, and 8), and self-guided sources (categories 6 and 7). Special attention will be given to category 6, which is the most common way to access Mindhelper.

The severity of mental health issues at T1, along with previous help-seeking behaviors, may influence both the use of Mindhelper and its effect on help-seeking intentions. To account for this, analyses will be stratified by symptoms of depression and anxiety (PHQ-4) and intentions of help seeking at T1. Among those with a mental health diagnosis, we will further stratify by T1 levels of impairment by mental health diagnosis within the last month (daily, weekly, more seldom than weekly, not affected, or do not know) and whether any treatment was received within the past month for the diagnosis (treatment received, on waitlist for treatment, or no treatment received).

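### Variation in effect is to be assessed by separate stratified analyses, although the stated hypothesis compares strata and the article names no between-stratum contrast

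*Protocol article*

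**What the plan says.** In the protocol article, the section on mental well-being and psychological functioning gives stratification as the means of assessing variation in effect by gender and parental education. It then adds baseline well-being: "In addition, we will stratify by mental well-being at T1, expecting Mindhelper to be most effective for participants with moderate mental well-being". Moderate means a T1 WHO-5 of 36–50. The comparison groups are 0–35 and above 50. The stratum above 50 is also to be used to look for a decline in well-being relative to control.

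The section on intentions of help seeking takes the same approach for an outcome labelled explorative: "analyses will be stratified by symptoms of depression and anxiety (PHQ-4) and intentions of help seeking at T1". Participants with a diagnosis are further split by impairment and by treatment.

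The sample size covers only the overall comparison at T2. Neither section names an interaction term, a heterogeneity test or a between-stratum contrast. The statistical analysis overview says that a detailed SAP has been published; it was not available for this review.

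**The concern.** The hypothesis is about a difference between effects: larger at 36–50 than in either neighbouring group. A model fitted within a stratum asks only whether there is an effect in that stratum. Three such answers set side by side do not test the hypothesis, so the method named and the question asked do not match.

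This matters because each stratum holds only a fraction of a sample sized for a 0.1 SD effect overall. With low power in each stratum, some will reach significance and others will not, even if the intervention works equally well in all of them. The authors expect a particular pattern, so a chance result that resembles it could be taken as confirmation.

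**Working it through.** **Inputs from the Sample Size Calculation and Study Design sections.** The effect is 1.94 WHO-5 points ("it is equal to an improved WHO-5 score of 1.94 points on average in the intervention group compared to the control group"). For the spread, the authors "assumed an SD of 19.4 at T1 among the intervention and control groups combined". Power is 0.80, the significance level is 0.05 and allocation is 1:1. On the number to be analysed, "at least 3142 participants were required".

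**Plan's own figure.** Per arm, n = 2 × (1.96 + 0.8416)² / (1.94/19.4)² = 2 × 7.849 / 0.01 ≈ 1570. The t-test version gives 1570.7, so 1571 per arm and 3142 in total. The sidedness is not stated, but two-sided reproduces the figure. Dividing 3142 by 0.64 gives 4909.4, hence the target of 4910.

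**Assumptions.**
- The Recruitment section reports 64.3% of the feasibility sample at risk on WHO-5. I take this as a score of 50 or below, which leaves 35.7% above 50. The cut-off is not given there.
- The share at 36–50 is not given. I use 15–35%, and the rest of the 64.3% falls in 0–35.
- The T1–T2 correlation r is not given. I use 0 (SD 19.4) and 0.5 (SD 19.4 × √0.75 = 16.8).
- The information analysed equals 3142 participants, and the true effect is 1.94 points in every stratum.

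**Formulas.**
- Stratum of n participants: SE = SD × √(4/n). Power = Φ(1.94/SE − 1.96) + Φ(−1.94/SE − 1.96).
- Mixed pattern (at least one stratum significant and at least one not): 1 − p₁p₂p₃ − (1−p₁)(1−p₂)(1−p₃).
- Only the moderate stratum significant: p₂(1−p₁)(1−p₃).
- Contrast of the moderate stratum with the rest: SE = SD × √(4/n_mod + 4/n_rest). Difference detectable with 80% power = 2.80 × SE.

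**Worked case: 25% moderate, r = 0.** In the moderate stratum n is about 786, SE = 19.4 × √(4/786) = 1.38 and power is 0.289. The other two strata have power 0.420 and 0.388. Mixed = 1 − 0.047 − 0.252 = 0.70. Moderate only = 0.289 × 0.580 × 0.612 = 0.10. Contrast SE = 19.4 × √(4/786 + 4/2356) = 1.60, so the detectable difference is 4.5 points.

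**Range.** Stratum order is 0–35 / 36–50 / above 50; sizes are rounded.

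| r | Moderate share | n per stratum | Power per stratum | Mixed | Moderate only | Detectable contrast |
|---|---|---|---|---|---|---|
| 0 | 15% | 1549 / 471 / 1122 | 0.50 / 0.19 / 0.39 | 0.72 | 0.06 | 5.4 |
| 0 | 25% | 1235 / 786 / 1122 | 0.42 / 0.29 / 0.39 | 0.70 | 0.10 | 4.5 |
| 0 | 35% | 921 / 1100 / 1122 | 0.33 / 0.38 / 0.39 | 0.70 | 0.16 | 4.1 |
| 0.5 | 15% | 1549 / 471 / 1122 | 0.62 / 0.24 / 0.49 | 0.78 | 0.05 | 4.7 |
| 0.5 | 25% | 1235 / 786 / 1122 | 0.53 / 0.37 / 0.49 | 0.75 | 0.09 | 3.9 |
| 0.5 | 35% | 921 / 1100 / 1122 | 0.42 / 0.48 / 0.49 | 0.75 | 0.14 | 3.5 |

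In simulation under the uniform effect, the moderate stratum had the largest estimate 33–38% of the time. Power of the contrast for a true difference of 1.94 points is 17–27% (21–34% with r = 0.5). For 3.88 points it is 52–76% (64–87%).

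**The case against.** The strongest reply is that this is a condensed article that points to a published SAP. Interaction terms and rules for reading subgroups commonly sit in a SAP. A reader might infer that the trial has no interaction test, but the documents do not support that: the article is silent, and nothing in it excludes such a test. This part of the objection stands, and the point is therefore confined to what the article names.

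A reader might also infer that the hypothesis cannot be tested at all. That does not follow either. The strata are disjoint groups of randomised participants, so their estimates can be contrasted without new data.

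Third, the article does not say that strata will be judged by separate significance, so the 70–78% figure is conditional on that reading. It also counts any mixed pattern. The one that would mimic the hypothesis most closely, moderate alone significant, occurs 5–16% of the time. This too stands. The planned baseline adjustment, however, does not help here: at r = 0.5 the mixed pattern becomes more frequent.

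Finally, the help-seeking strata are a weaker example, since the outcome is explorative and no stratum is predicted to benefit most.

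None of this removes the mismatch. The article names specific methods for its other questions. For variation in effect it names stratification alone, beside a comparative hypothesis.

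**Conclusion.** The point holds for the article's wording. Stratified analyses are named as the way to assess variation in effect, a directional comparison between strata is stated, and no between-stratum contrast is given. Separate stratum estimates do not answer that question. Whether the SAP closes the gap cannot be judged here.

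The size depends on assumed stratum shares, on the assumed correlation and on strata being compared by separate significance. Within those limits the conclusion is stable: a misleading mixed pattern is more likely than not in every case tabulated. The primary comparison at T2 is unaffected, so this should be corrected but does not threaten the trial's main result.

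**What to change.** Unless the published SAP already does so:

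- Fit the planned linear model in all participants with arm-by-subgroup interaction terms for T1 WHO-5, gender and parental education.
- For T1 WHO-5, test the pre-stated contrast of 36–50 against the other two groups.
- Report stratum effects with confidence intervals from that model.
- Base any claim of differing effects on the interaction, labelled exploratory, and apply the same rule to the help-seeking strata.

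The check for decline above 50 is a within-stratum question and can stay. If the SAP already specifies the interaction, one sentence saying so in the article is enough.

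The change needs no new data, only wording settled before outcome analysis and unblinding. The cost is in what can be claimed. The contrast has 80% power only for differences about two to three times the 1.94 points for which the trial is sized, so the hypothesis will rarely be confirmed and subgroup claims become harder to make. A non-significant interaction should not be read as evidence of equal effects.

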#### The Effects of Mindhelper on Intentions of Help Seeking

To evaluate the impact of Mindhelper on help-seeking intentions, we will compare scores on the constructed scale between the intervention and control group at T3, adjusted for T1 values. Potential long-term effects will be assessed at T4 using a model accounting for repeated measures. We selected T3 for this evaluation because we hypothesize that changes in help-seeking intentions take longer to manifest compared to the primary and secondary outcomes.

The 8 categories of support will be assessed separately. Furthermore, we will categorize the sources into 3 groups: informal sources (categories 1, 2, and 3), formal sources (categories 4, 5, and 8), and self-guided sources (categories 6 and 7). Special attention will be given to category 6, which is the most common way to access Mindhelper.

The severity of mental health issues at T1, along with previous help-seeking behaviors, may influence both the use of Mindhelper and its effect on help-seeking intentions. To account for this, analyses will be stratified by symptoms of depression and anxiety (PHQ-4) and intentions of help seeking at T1. Among those with a mental health diagnosis, we will further stratify by T1 levels of impairment by mental health diagnosis within the last month (daily, weekly, more seldom than weekly, not affected, or do not know) and whether any treatment was received within the past month for the diagnosis (treatment received, on waitlist for treatment, or no treatment received).

#### The Effect of Mindhelper on Body Appreciation

The effect of Mindhelper on body appreciation will be assessed by comparing body appreciation scores (measured using the BAS-2 Short Form [42]) between the intervention and control groups at T2, using a linear regression model (if model assumptions are met) and adjusted for T1 scores. If model assumptions are met, potential long-term effects will be evaluated at T3 and T4 using a repeated measures linear regression model.

In addition, we will explore the mediating role of mental well-being and psychological function (WHO-5 and SWEMWBS) in the relationship between Mindhelper and body appreciation. The mediation analysis will estimate the natural direct and indirect effects [48], providing insights into how mental well-being and psychological function may explain any influence of Mindhelper on body appreciation.

#### Cost-Effectiveness Analysis

The cost-effectiveness analysis will be performed by constructing a standard incremental cost-effectiveness ratio (ICER) expressing the additional cost per mean mental well-being score, measured by WHO-5, obtained from the randomization to Mindhelper compared with standard care [49]. The analysis will apply standard techniques from economic evaluation aimed at estimating costs per quality-adjusted life years gained. The results from this analysis will contribute to the evidence-based economic evaluation of interventions aimed at increasing mental health and well-being.

Incremental estimates of costs and mental well-being scores obtained will be assessed in a regression model. To examine the second-order uncertainty of the estimated ICERs, a probabilistic sensitivity analysis using a 5000 bootstrap resample with a 95% CI will be conducted. Cost-effectiveness planes illustrating the resampled ICERs and cost-effectiveness acceptability curves at T2 to T4 will be constructed to show the probability that the intervention is cost-effective given varying threshold values for an additional change in the mean mental well-being score obtained. No standardized fixed threshold for the value of an additional mean mental well-being score obtained from a new health intervention exists. Therefore, the probability of cost-effectiveness will be investigated for several thresholds, for example, values ranging from 0 to DKK 500,000 (US $78,038.43).

Both potential health care savings and direct costs of delivering the intervention will be included in the analysis. Information on self-reported all-cause demand for acute health care services, general practitioner visits, use, and absence from employment in the project period will be gathered from surveys. To operationalize this in monetary terms, the average unit cost of acute health care use and average hourly wage earnings depending on gender and age in Denmark will be used in the economic evaluation. For the intervention group, operating costs related to Mindhelper will also be included based on the overall cost per user. These costs cover development, maintenance, and technical support for the service. Cost estimates will be calculated based on list prices from health care providers, and scenarios of changes in the number of users will be explored.

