**Methods:**

We will recruit 4910 people aged between 15 and 25 years via social media and randomized and allocated to an intervention group (receiving information about Mindhelper) or a control group (no information about Mindhelper). Outcomes are self-assessed and collected at baseline and 2, 6, and 12 weeks after randomization through online surveys and analyzed using the intention-to-treat approach. Qualitative interviews with intervention group participants will provide complementary insights, and a cost-effectiveness analysis will also be conducted.

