Throughout its development and dissemination phase, Mindhelper has adopted a participatory approach, co-designing its resources with young people, parents, teachers, school counselors, youth workers, psychologists in community care, general practitioners, and youth mental health experts. More than 300 young people have participated in workshops, user panels, and content production teams. Iterative coproduction methods, based on the core principles of design thinking (understanding, defining, ideating, prototyping, and refining), have been crucial in ensuring the service remains relevant and useful to young people [26-28].

Since January 2019, Mindhelper has received permanent funding through a joint agreement between the 5 Danish regions and has been freely available and disseminated to young people and youth mental health professionals across the country. Mindhelper receives approximately 1 million visits a year [29]. Mindhelper’s primary target group is people aged between 13 and 20 years; however, it also includes adults, parents, and youth mental health professionals [29].

In 2024, Mindhelper launched their first mobile app named Ro (Ro is Danish for calm), aiming to reduce stress and increase everyday calmness. The app is free to use and may be downloaded on Android smartphones and iPhones. In this paper, the Mindhelper website and the app Ro will be referred to commonly as “Mindhelper.”

The research team was not involved in developing Mindhelper or its maintenance or promotion. Partnering with the Centre for Digital Psychiatry meant that the service tested builds on evidence-based information and is built by an expert team. Furthermore, the service is sustainable (independent of research funds) compared to most services tested, as Mindhelper was constructed and is funded and used independently of this study.

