The recruitment material states that the study is evaluating a mental health promotion website for young people, but does not mention Mindhelper specifically, to avoid influencing the control group’s use. Mindhelper remains publicly accessible during the study, and there is no way to ban access of participants from the control group. However, our feasibility study found that very few control group participants accessed the website, suggesting this is not a significant concern [18].

The intervention group participants may use the service as much as they like. Participants in the intervention group and control group may continue with any usual care they receive in addition to the trial. Nonresponse is minimized by sending up to 2 reminders.

At T3, participants in the intervention group will be invited to participate in 2 interviews (when responding to the survey): the 1st close to T3 and a follow-up interview approximately 12 weeks later. Further details of the qualitative part of the study are presented in the section “Qualitative Contributions.”

At the end of each survey, it is emphasized that the research team does not provide counseling or treatment and will not contact anyone based on their survey responses. Participants (in the intervention and control group) are strongly encouraged to seek help and support if they experience distress or require assistance and are directed to counseling services, including Børnetelefonen and HØRT (Danish consulting services for young people). Furthermore, in cases of acute suicidal crises, they are encouraged to contact Livslinien (a Danish service for people with suicidal thoughts) or emergency services.

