**Use of Mindhelper**					
	Digital behavior when feeling down	✓	✓	✓	✓
	Use of Mindhelper (in the intervention group)		✓	✓	✓
	Thoughts on the SMS text message campaign (in the intervention group)		✓	✓	✓
	Familiarity with or use of Mindhelper and Ro (at T1 for all participants and at T4 for the control group)	✓			✓

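### Mindhelper's operating cost is charged to the intervention arm only, although controls have open access and their use is measured, so that cost component is not net of control use as the WHO-5 effect is

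*Protocol article*

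**What the plan says.** The Cost-Effectiveness Analysis section of the protocol article defines the incremental cost-effectiveness ratio (ICER) as additional cost per WHO-5 score "obtained from the randomization to Mindhelper compared with standard care". On the cost side it says: "For the intervention group, operating costs related to Mindhelper will also be included based on the overall cost per user". It adds: "These costs cover development, maintenance, and technical support for the service". It gives no corresponding rule for a control participant who uses the service.

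Other sections make clear that controls can use it. Under Intervention: Mindhelper, the service is permanently funded since January 2019 and "has been freely available and disseminated to young people and youth mental health professionals across the country". Under Study Design: "Mindhelper remains publicly accessible during the study, and there is no way to ban access of participants from the control group". The same section says: "Participants in the intervention group and control group may continue with any usual care they receive in addition to the trial". Strengths and Limitations names open access as something that could dilute the difference between the groups.

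Control use is also recorded. Table 1 lists "Familiarity with or use of Mindhelper and Ro (at T1 for all participants and at T4 for the control group"). The overview of the Planned Statistical Analysis uses self-reported use at T4 in both arms for the complier average causal effect. The Discussion gives the schedule as T2 to T4 for the intervention group and T1 and T4 for controls.

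**The concern.** An ICER is interpretable only if its numerator and denominator describe the same contrast. Here the denominator is the intention-to-treat WHO-5 difference, in which any benefit that controls draw from Mindhelper has already been subtracted. The operating-cost part of the numerator has no such subtraction: a control who uses the site contributes to the control mean on WHO-5 and is charged nothing. The trial would count control use when estimating the complier effect and ignore it when costing.

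The comparator label adds to this. Usual care in both arms already includes open access to Mindhelper, so calling the comparator standard care does not justify a zero Mindhelper cost in controls. At stake is a cost component that is tilted against the intervention, and a result whose comparator is not described as it was in the trial.

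**Working it through.** The article states no cost per user, no use rates and no ICER, so there is no figure of the plan's to reproduce. The check is algebraic, with use rates as assumptions.

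**Notation.** c = overall cost per user; pI, pC = share of participants using Mindhelper in the intervention and control arms; Δ = WHO-5 difference between randomised arms.

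**Step 1. Operating-cost difference per randomised participant.**
- Matched to the randomised contrast: c·pI − c·pC = c·(pI − pC).
- Stated rule, if users in the intervention arm are charged: c·pI.
- Ratio of stated to matched: pI/(pI − pC). It equals 1 only if no control uses Mindhelper.

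**Step 2. Values of that ratio (assumed rates).**

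| pI | pC = 1% | pC = 2% | pC = 5% |
|---|---|---|---|
| 20% | 0.20/0.19 = 1.05 | 0.20/0.18 = 1.11 | 0.20/0.15 = 1.33 |
| 40% | 0.40/0.39 = 1.03 | 0.40/0.38 = 1.05 | 0.40/0.35 = 1.14 |
| 80% | 0.80/0.79 = 1.01 | 0.80/0.78 = 1.03 | 0.80/0.75 = 1.07 |

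The ratio depends on control use relative to intervention use. It is close to 1 when control use is rare and the SMS campaign works, and grows when intervention use is also low.

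**Step 3. What this does to the ICER.** The stated operating cost exceeds the matched one by c·pI − c·(pI − pC) = c·pC per participant, so the ICER shifts by c·pC/Δ. At the effect used for the sample size, Δ = 1.94 points, the shift per WHO-5 point is 0.01c/1.94 = 0.005c at pC = 1%, 0.02c/1.94 = 0.010c at 2%, and 0.05c/1.94 = 0.026c at 5%. Since c is not given, and health care use and absence (both collected in both arms) also enter the numerator, the proportional change in the total cost difference cannot be computed.

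**Step 4. The other possible reading of the cost sentence.** If every intervention participant were charged, the stated component would be c and the ratio 1/(pI − pC): for example 1/0.35 = 2.86 at pI = 40%, pC = 5%. The sentence does not say that this is intended.

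**Step 5. Do the planned sensitivity analyses cover this?** Scenarios for the number of users change c, not which arm bears it. The bootstrap describes sampling uncertainty around the chosen rule and leaves the rule itself unchanged.

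**The case against.** The strongest reply is about size. The article says twice that very few controls reached the site in the feasibility study. At 1% to 2% control use the ratio is near 1 unless intervention use is low, and the very low intervention use seen in that study came from giving participants a link only; 29 SMS messages have since been added to raise it. This stands, with the caveat that the article itself says it does not yet know whether the campaign is sufficient.

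Second, only one cost component is affected. A reader might infer that the total cost difference, and with it the ICER, is materially overstated. The documents do not support that, because they give no unit cost.

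Third, a reader might infer an error of several-fold from charging non-users in the intervention arm. That rests on a reading the cost sentence does not state, and who counts as a user is a detail an article may leave to the full plan.

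Fourth, an average per-user cost that includes development is not the incremental cost of prompting people towards a service that is already funded. Under that contrast, fixed costs arise in both arms whoever visits. This also stands: the ratio above measures the inconsistency within the plan's own per-user costing, and charging users in both arms does not by itself turn average cost into marginal cost.

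Fifth, open access and continued usual care are disclosed, and the article says that it evaluates the SMS campaign and Mindhelper together. A reader might take the ICER as answering whether Mindhelper should be funded at all; the cost-effectiveness section makes no such claim. Disclosing dilution of the effect does not, however, settle how control use is costed.

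**Conclusion.** The point holds for the operating-cost component. As written, that component omits control use while the WHO-5 difference is net of it, so it is biased against Mindhelper whenever any control uses the service. If intervention users are charged, the excess is about 3% to 5% at 40% intervention use and 1% to 2% control use, and 33% at 20% and 5%. All these rates are assumptions, and the article's own expectation of very few control users points to the lower end for pC. The effect on the total cost difference is unknown and may be small. The primary WHO-5 analysis is not touched. The comparator needs a more exact description; standard care is not false, but here it includes unprompted access to Mindhelper.

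**What to change.** Make these changes in the cost-effectiveness plan before outcome data are analysed:

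1. Apply the same per-user operating cost to every participant who reports using Mindhelper or Ro, in either arm: T2 to T4 reports in the intervention arm, the T4 report in controls. Count use only, since the Table 1 item also covers familiarity.
2. State an assumption, with a sensitivity range, for control use at T2 and T3, because acceptability curves are planned from T2 to T4 and controls are not asked at those two points. Do the same for T4 non-responders.
3. Show two scenarios: every intervention participant charged, and development and other fixed costs common to both arms excluded.
4. Describe the comparator as usual care with unprompted open access to Mindhelper, in the ICER definition and in the conclusions.

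The cost is a revised cost variable, a few scenario runs and some wording; no new data are needed. The downside is that use is self-reported and the timing of control use before T4 is unknown, so the T2 and T3 results will rest partly on assumption.
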